### Gut Microbial Profiling

Metagenomic sequencing will be used to analyze the spectrum of specific intestinal flora in NSTEACS patients after treatment with SQSX, revealing the mechanism of pharmacological effect from the intestinal flora perspective. The fecal collection kit and proper instruction for stool collection will be prepared for participants. Fecal samples will be stored in a laboratory freezer (−80°C) until metagenomic sequencing. The main steps of metagenomic sequencing are as follows: (1) genomic DNA is extracted and purified from feces using the QIAamp DNA kit; (2) genomic DNA is then fragmented to 350-bp by a Covaris crusher; (3) terminal repair, A-tailed, sequencing connector and other steps are performed to prepare a short cDNA library; (4) the library is then sequenced with Illumina Hiseq; (5) the sequence is assembled and finally analyzed for species and functional annotation.

### Randomization and Blinding

The randomization will be conducted by the Institute of Clinical Pharmacology of Xiyuan Hospital, China Academy of Chinese Medical Sciences. The SAS software-generated random sequencing in blocks of four was used for randomization. Eligible patients are randomized into the SQSX or control group on a 1:1 basis. Researchers and outcome evaluators involved in this study know nothing about the details of the randomization sequence. All patients and physicians will be unaware of treatment allocation until the end of the study. Urgent letters revealing group and treatment allocation have been prepared. If an emergency occurs, blind breaking and urgent measures may need.

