### Inclusion Criteria

Subjects who meet all of the following criteria are eligible to participate in the study: (1) diagnosed as unstable angina (UA) or non-ST segment elevated myocardial infarction (NSTEMI) according to the 2015 ESC guidelines for the management of NSTEACS (22); (2) diagnosed as the TCM syndrome of Qi deficiency and blood stasis according to the Guiding Principles For Clinical Research Of New Chinese Medicines (23); (3) age 40–60 years; (4) heart function is Killip grade I-II for subjects diagnosed as NSTEMI; (5) in-hospital patients; (6) written informed consent is obtained.

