**Patients**				
Inclusion/exclusion criteria		×		
Informed consent	×			
General information ^a)^	×			
Medical and treatment history recording	×			
Randomization and allocation	×			

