### Sample Size Calculation

The sample size was estimated using hs-CRP. Currently, the hs-CRP of NSTEACS decreased from 5.30 mg/L to 3.74 mg/L after 14 days of conventional treatment, with a decline rate of 29.43% (26). The hypothesis is that the treatment group could reduce the hs-CRP of NSTEACS by 35%. With a type I error rate of α = 0.05 and a power of 80% (a type II error rate of β = 0.2), one arm requires a sample size of 27. With a 20% drop-out rate, we have to recruit a total of 66 patients. The following is the formula for calculating sample size (27):

$$\begin{array}{l} \text{n}=2{\left[\frac{\left({\text{u}}_{\alpha }+{\text{u}}_{\beta }\right)}{\delta /\sigma }\right]}^{2}+\frac{1}{4}u_{\alpha }^{2} \end{array}$$

n, is the sample size required in each group, δ = μ_1_-μ_2_, is the difference between means of two groups, σ, is the standard deviation, u_α_ and u_β_ are the values of u corresponding to the test level α and type II error probability β, respectively.

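### Diagnosis (UA or NSTEMI) enters the hs-CRP analysis only if imbalance is seen; fixing it in the primary model beforehand would protect precision at almost no cost

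*Protocol article*

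**What the plan says.** All places are in the protocol article.

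- **Inclusion Criteria.** A patient qualifies when "diagnosed as unstable angina (UA) or non-ST segment elevated myocardial infarction (NSTEMI) according to the 2015 ESC guidelines". The expected share of each diagnosis is not given. One criterion, Killip grade, applies to NSTEMI only.
- **Randomization and Blinding.** "The SAS software-generated random sequencing in blocks of four was used for randomization", and "Eligible patients are randomized into the SQSX or control group on a 1:1 basis". No stratification factor is mentioned.
- **Sample Size Calculation.** One course is used for the whole population: "the hs-CRP of NSTEACS decreased from 5.30 mg/L to 3.74 mg/L after 14 days of conventional treatment". The assumed effect follows: "The hypothesis is that the treatment group could reduce the hs-CRP of NSTEACS by 35" per cent. The result is 27 per arm, raised to 66 in total for drop-out. The formula contains a standard deviation, but no value is given for it.
- **Statistical Analyses.** The primary outcome is the change in hs-CRP. The groups are compared by a Student t test, or by the Wilcoxon rank-sum test if normality or equal variance fails. Adjustment is conditional on baseline imbalance; the methods listed for it are Cox regression, logistic regression and analysis of covariance. A linear mixed-effects model is planned for the repeated measures. No covariate is named and no definition of imbalance is given.
- **Trial Status.** Twenty participants had completed follow-up and no analysis had been done.

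**The concern.** The diagnosis is known at entry and may predict the outcome: if infarction brings its own rise and fall in hs-CRP, the two diagnoses will change by different amounts over 14 days. Adjusting for baseline hs-CRP alone need not capture this, since the same baseline value could be a settled level in one patient and a point on a moving curve in another. The documents do not establish that the courses differ; it is an assumption here.

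If it is true, two things are at stake. Variation due to diagnosis stays in the error term of the unadjusted test, in a small trial planned on a small difference. And because adjustment depends on the imbalance observed, by an undefined criterion, the model that yields the primary result is chosen only after baseline data are inspected.

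**Working it through.** **1. Design difference.** From the Sample Size Calculation section: conventional fall = 5.30 − 3.74 = 1.56 mg/L (1.56 / 5.30 = 29.43%, as stated). Fall under SQSX = 0.35 × 5.30 = 1.855 mg/L. Difference δ = 1.855 − 1.56 = **0.295 mg/L**.

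**2. SD implied by 27 per arm.** The article's formula is n = 2[(u_α + u_β)/(δ/σ)]² + u_α²/4. Take u_α = 1.96 (two-sided 5%), u_β = 0.842 (80% power) and n = 27, and solve for σ:

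σ = 0.295 / √[2 × 2.802² / (27 − 0.96)] ≈ **0.38 mg/L**.

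Putting σ = 0.38 back gives n = 27.0. The article's 27 cannot be checked forwards, because no SD is given. The total does follow: 27 × 1.2 = 32.4, so 33 per arm and 66 in all.

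**3. Chance difference in NSTEMI share.** With 33 per arm and NSTEMI share p, the SD of the between-arm difference in share is √[2p(1 − p)/33]. The share is an assumption, taken as 20–50%.

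| p | SD of difference in share |
|---|---|
| 0.2 | 0.098 |
| 0.3 | 0.113 |
| 0.4 | 0.121 |
| 0.5 | 0.123 |

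Simulating blocks of four with 66 patients reproduces these values. A difference of 10 points or more occurs in 30% to 39% of randomisations.

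**4. Resulting shift in the hs-CRP comparison.** Assume a mean fall in UA of 0.5 to 1.3 mg/L and hold the pooled fall at 1.56 mg/L. The NSTEMI fall is then [1.56 − (1 − p) × UA fall]/p, the gap between diagnoses is (1.56 − UA fall)/p, and the 1-SD shift is the gap times the SD from step 3.

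| p | UA fall (mg/L) | Gap (mg/L) | 1-SD shift (mg/L) | Chance that the shift exceeds 0.295 |
|---|---|---|---|---|
| 0.2 | 0.5 | 5.30 | 0.52 | 61% |
| 0.4 | 0.5 | 2.65 | 0.32 | 37% |
| 0.4 | 1.0 | 1.40 | 0.17 | 9% |
| 0.4 | 1.3 | 0.65 | 0.08 | under 0.1% |
| 0.5 | 1.3 | 0.52 | 0.06 | under 0.1% |

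The range is **0.06 to 0.52 mg/L**. The top corner is strained: it implies a mean NSTEMI fall of 5.8 mg/L, above the pooled baseline of 5.30 mg/L.

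**5. Cap set by the plan's own SD.** Diagnosis alone contributes an SD of gap × √[p(1 − p)] to the outcome, which cannot exceed the total SD. If the total is 0.38, the 1-SD shift is at most 0.38 × √(2/33) = **0.094 mg/L**, whatever the share. The 1.96-SD shift is at most 0.18 mg/L. As fractions of 0.295 these are 32% and 61%, and a shift of 0.295 would be an event of about 3.2 SD (probability about 0.002).

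**6. The two scales conflict.** A gap of 2.65 mg/L at p = 0.4 gives a between-diagnosis SD of 2.65 × √0.24 = 1.30 mg/L, more than three times 0.38. So the larger shifts in step 4 and the planned sample size cannot both be right.

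**The case against.** The strongest reply is that this is ordinary sampling error. The step 4 formula is the between-diagnosis SD times √(2/33), which is simply that component's part of the usual standard error. A two-group test estimates its SD from patients of both diagnoses and so already allows for it. Randomisation without strata is valid. **This stands.** A reader might infer that chance imbalance in diagnosis could by itself create or hide the whole assumed effect. The documents do not support that: they give neither the mix nor the hs-CRP course by diagnosis, shifts of that size need the wider assumed gaps, and those gaps contradict the SD implied by the sample size.

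Second, a condensed article that names no stratification factor does not show that none was used. **This stands too.** A reader might take the list to be unstratified as a fact; the article only leaves it undescribed. The fix does not depend on the answer, since a stratified design would also call for diagnosis in the model.

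Third, adjustment is already planned, and naming covariates is commonly left to an analysis plan that is not shown. **This stands in part.** The absence of a covariate list is no fault. But the article does state a rule, that adjustment waits on observed imbalance, and it is this rule that leaves the primary model open. Two of the methods listed, Cox and logistic regression, do not suit a continuous change score, so the list does not settle the model either.

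In the other direction, the 0.38 mg/L cap is not a firm bound. It is back-calculated and very small beside a baseline of 5.30 mg/L. If the true SD is larger, diagnosis could matter more. But the main problem would then be the sample size, which a diagnosis term would not repair.

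**Conclusion.** The point holds as one of precision and pre-specification. Both diagnoses are enrolled, no stratification factor is described, and the stated primary comparison is unadjusted unless imbalance is observed. Provided hs-CRP course differs by diagnosis, leaving diagnosis out loses precision, and the conditional rule makes the primary model data-dependent. It is not a source of bias, and it does not invalidate the randomisation or the unadjusted test.

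The size is uncertain. It runs over the whole range in step 4 if the assumed shares and UA falls are accepted, and is limited to the step 5 cap if the plan's implied SD is right. The case for change rests less on any single figure than on the low cost of removing an avoidable loss while no analysis has been done.

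**What to change.** In Statistical Analyses, for the primary outcome, replace the adjustment triggered by imbalance with one pre-specified hs-CRP model: analysis of covariance, or the linear mixed-effects model already planned. Include diagnosis at entry (UA or NSTEMI) as a fixed factor whatever balance is observed, and set this down before any analysis. The cost is a change of wording and one degree of freedom; diagnosis is already established for eligibility, so no new data are needed.

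Stratifying the remaining patients by diagnosis is optional. It would need new lists and kit re-numbering part-way through the trial, and the model change stands without it.

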### Data Management and Monitoring

All participant data on the CRF will be input into the clinical trial data management system. To ensure the authenticity, accuracy and completeness of data, several effective procedures are used. First, data cleaning will consider missing data, questionable values and inconsistent dates. After that, the source data will be verified by the supervisor to check for consistency. Third, manual checks. Clinical monitors will be appointed by the quality assurance department of Xiyuan Hospital, China Academy of Chinese Medical Sciences to undertake regular monitoring visits on the trial's progress and completion.

### Investigator Training and Quality Control

All investigators engaged in the study will be trained in standard operating procedure (SOP). The training includes screening of eligible subjects, standard collection and storage procedures for stool samples, and the use of evaluation scales, etc. All results will be reported by outcome evaluators trained in SOP standards to ensure their reliability and validity. In addition, to ensure relevant clinical data is collected as planned, researchers will establish close connection with patients through phone and WeChat groups.

### Sample Size Calculation

The sample size was estimated using hs-CRP. Currently, the hs-CRP of NSTEACS decreased from 5.30 mg/L to 3.74 mg/L after 14 days of conventional treatment, with a decline rate of 29.43% (26). The hypothesis is that the treatment group could reduce the hs-CRP of NSTEACS by 35%. With a type I error rate of α = 0.05 and a power of 80% (a type II error rate of β = 0.2), one arm requires a sample size of 27. With a 20% drop-out rate, we have to recruit a total of 66 patients. The following is the formula for calculating sample size (27):

$$\begin{array}{l} \text{n}=2{\left[\frac{\left({\text{u}}_{\alpha }+{\text{u}}_{\beta }\right)}{\delta /\sigma }\right]}^{2}+\frac{1}{4}u_{\alpha }^{2} \end{array}$$

n, is the sample size required in each group, δ = μ_1_-μ_2_, is the difference between means of two groups, σ, is the standard deviation, u_α_ and u_β_ are the values of u corresponding to the test level α and type II error probability β, respectively.

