## Methods/Design

### Study Design

The randomized, double-blinded and placebo-controlled trial was endorsed by the Ethics Committee of Xiyuan Hospital, China Academy of Chinese Medical Sciences (Version No. XYYY-ASKY-1.1, January 1, 2021), and registered in the Chinese Clinical Trials Registry (ChiCTR2000029226). Our study conforms to the Helsinki Declaration and the Good Clinical Practice guidelines. It follows the Consolidated Standards of Reporting Trials Extension for Chinese Herbal Medicine Formulas 2017 (CONSORT-CHM Formulas 2017)recommendations and the Standard Protocol Items: Recommendations for Interventional Trials statements (SPIRIT) (20, 21). The study is currently underway at the Xiyuan Hospital, China Academy of Chinese Medical Sciences. Altogether 66 participants will be enrolled and randomly allocated to two groups. All participants will receive their respective interventions for 14 days. The clinical evaluations will be conducted at baseline (Visit 1), days 7 ± 3 (Visit 2) and 14 ± 3 (Visit 3), respectively. Figure 1 depicts a schematic of the study design.

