### Statistical Analyses

An independent biostatistician will perform statistical analysis. The result of recruitment, the specific reasons for data missing and the distribution of each statistical analysis data set will be described. The primary outcome, the change values of hs-CRP from recruitment to day 7 ± 3, day 14 ± 3 and the day of revascularization, and the secondary outcome, the change scores in five dimensions of SAQ at the same time, are both continuous variables. For comparison between groups, the continuous variables will be described using means ± SD, median, interquartile range, etc., and the Shapiro-Wilk normality test and Levene test for variance homogeneity will be performed. A Student *t* test will be used to compare two groups that have a normal distribution with homogeneous variance, otherwise the Wilcoxon rank-sum test will be used. When some continuous variables are converted into categorical variables, these categorical variables will be described using rates, and the chi-square test or Fisher's exact probability method will be used. For comparison within groups, the paired *t* test or Wilcoxon signed-rank test will be used for continuous variables and the McNemar test for categorical variables. If there are baseline imbalances, Cox regression analysis, logistic regression and multivariate analysis of covariance will be used to adjust confounding variables. The longitudinal data with repeated measures will be analyzed using the linear mixed-effects model to assess associations. The safety analysis will tabulate a detailed description of the adverse reactions, adverse events and serious adverse events and compare the difference in incidence between two groups using Fisher's exact probability method. A difference of *P* < 0.05 at two-tailed test will be considered statistically significant in all analyses. The statistical analyses will be performed using SAS software version 9.4 (SAS Institute, Cary, NC, USA).

After metagenomic sequencing is completed, microbiota community structures will be compared at different taxonomic levels. The abundance and diversity of intestinal flora will be analyzed. The relationship between microbiota composition and clinical outcomes will be investigated using univariate and multivariate linear and nonlinear mixed and regression models. Gene annotation will be conducted to study the function of the intestinal flora.

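### At the stated 20% drop-out, 66 recruits leave an expected 26.4 patients per arm, just below the 27 that the sample-size section requires

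*Protocol article*

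**What the plan says.** The Sample Size Calculation section of the protocol article sets a type I error rate of 0.05 and 80% power, and concludes that "one arm requires a sample size of 27". The next sentence adds the attrition allowance: "With a 20% drop-out rate, we have to recruit a total of 66 patients". The section prints the formula for the number per group but not the step from 27 per arm to 66.

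The same total appears in the Abstract and under Study Design ("Altogether 66 participants will be enrolled and randomly allocated to two groups"). Randomization and Blinding fixes the split: "Eligible patients are randomized into the SQSX or control group on a 1:1 basis". So 66 recruits means 33 per arm. Two-sided testing is stated under Statistical Analyses, not in the sample-size section: "A difference of *P* < 0.05 at two-tailed test will be considered statistically significant in all analyses".

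**The concern.** Two consecutive sentences give a required number, a loss rate and a recruitment total, and the three do not fit together. If 20% of the recruits are lost, 33 per arm does not leave 27. A common cause is to add 20% of the completers when the aim is to allow for losing 20% of the recruits. The first multiplies by 1.2 and the second divides by 0.8.

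At stake is whether the planned total delivers the evaluable number that the plan gives as its own requirement. The plan has no visible margin, because 27 is the figure it needs for 80% power, and the Discussion already concedes that the sample is small.

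**Working it through.** **Inputs**
- Required per arm: 27, so 54 in total (Sample Size Calculation).
- Drop-out: 20% (same section).
- Recruits: 66 (same section, Abstract, Study Design).
- Allocation 1:1, so 33 per arm (Randomization and Blinding).
- α = 0.05 and power 80% (Sample Size Calculation); two-sided (Statistical Analyses).

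The figure of 27 is taken as given. It cannot be recomputed, because the section defines the standard deviation but gives no value for it. The drop-out step does not need that value.

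**Reproducing 66**
- Multiply per arm: 27 × 1.2 = 32.4, rounded up to 33, doubled to **66**. Exact match.
- Divide per arm: 27 / 0.8 = 33.75, rounded up to 34, doubled to **68**.
- Multiply the total: 54 × 1.2 = 64.8, rounded up to 65.
- Divide the total: 54 / 0.8 = 67.5, rounded up to 68.

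Of these four routes from 27, only multiplication by 1.2 with rounding per arm gives 66.

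**What 66 delivers**
- Expected completers: 66 × 0.8 = 52.8, or 33 × 0.8 = 26.4 per arm. The shortfall is 27 − 26.4 = 0.6 per arm.
- Largest drop-out that still leaves 27 of 33: 1 − 27/33 = 18.2%.
- For comparison, 68 × 0.8 = 54.4, or 27.2 per arm.

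**Effect on power**

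The article's formula is n = 2[(u_α + u_β)/(δ/σ)]² + u_α²/4. Assume that n = 27 gives exactly 80% power, two-sided, with u_α = 1.960 and u_β = 0.842. Then u_α²/4 = 0.960 and

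δ/σ = 2.802 × √(2/(27 − 0.960)) = 0.776.

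Power at another n is Φ(0.776 × √((n − 0.960)/2) − 1.960):

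| n per arm | Power, two-sided | Power, one-sided (recalibrated) |
|---|---|---|
| 27 | 80.0% | 80.0% |
| 26.4 | 79.1% | 79.2% |
| 26 | 78.4% | 78.6% |

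**If 27 was rounded up from a lower value**

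Suppose the unrounded n lay between 26.0 and 26.4. Recalibrating the same formula at the lower end, power at 26.4 per arm is

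Φ(2.802 × √((26.4 − 0.960)/(26.0 − 0.960)) − 1.960) = 80.6%.

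At the upper end it is 80.0% by construction.

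**Chance of reaching 54 completers**

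With independent drop-out at 20%, the binomial probability of at least 54 completers in total is 42.7% with 66 recruits and 61.8% with 68.

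**The case against.** **The cause is inferred.** The article does not show the inflation step, and a correct division can also give 66. An unrounded n between 26 and 26.4 would be printed as 27, and dividing it by 0.8 gives 32.5 to 33.0, so 33 per arm. Without a standard deviation this cannot be excluded. The objection stands against stating the multiplication as fact. It does not reconcile the printed figures, because the stated requirement is 27 and 33 × 0.8 is 26.4.

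**Power may not suffer.** A reader might infer that 80% power cannot hold with 66 recruits and 20% loss. The document does not support that. If 27 was rounded up from 26.0 to 26.4, power at 26.4 per arm is about 80.0 to 80.6%. The figure of 79% needs 27 to be exact.

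**The shortfall is an expectation.** A reader might also infer that the trial is certain to miss its target. It is not: at 20% drop-out, 66 recruits still reach 54 completers about 43% of the time, and 68 recruits miss it about 38% of the time.

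**Dropouts are to be analysed.** Withdrawal, Dropout, and Discontinuation says that dropouts' data enter the analysis, and Statistical Analyses includes a mixed-effects model that could use a day-7 value when day 14 is missing. This softens the practical loss. It does not remove the inconsistency, because the sample-size section itself treats dropouts as lost when it inflates for them, and a t test on the day-14 change would still lose patients with no day-14 value.

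**It is very small.** The difference is two recruits and about one point of power, against a drop-out rate that is itself a round planning figure. That stands and sets the weight of the point.

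**Conclusion.** The point holds as a minor arithmetic inconsistency. On the article's own figures, 66 recruits with 20% drop-out leave an expected 26.4 per arm against a stated requirement of 27. Multiplication by 1.2 is the likely explanation, but it is not documented.

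The size is 0.6 patients per arm, or two recruits, and the total covers 18.2% drop-out instead of 20%. Power falls from 80% to about 79% at 26.4 per arm, or 78.4% at 26, on the assumption that 27 per arm gives exactly 80%. With rounding the loss may be smaller or nil. The document does not support a claim that the trial is materially underpowered for this reason, nor that a shortfall is certain.

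The conclusion takes 27 as correct and counts every dropout as lost to the powered comparison, as the sample-size section does.

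**What to change.** Change one sentence in Sample Size Calculation so that the three figures agree. Either of two restatements leaves recruitment at 66:

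- Keep 66 and 27 per arm, and restate the drop-out allowance as about 18%.
- Keep 66 and 20%, and state that about 26 evaluable patients per arm are expected, with about 78 to 79% power if 27 per arm corresponds to exactly 80%.

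If the sponsor chooses to keep both 27 and 20%, the total is 68, which is two more patients and a change wherever 66 appears. It also makes 17 full blocks of four, but a part-filled last block at 66 is not an error and is no reason on its own to change the total.

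Whichever is chosen, the sentence should show the inflation step. The restatements cost one sentence and a slightly less favourable allowance or power. Trial Status reports 20 participants through follow-up and no analysis so far, so on that account the correction can be made without reference to results.
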